**Inclusion criteria:**

The only inclusion criteria are that the men should have a semen quality below semen donor level and be otherwise healthy.

**Exclusion criteria:**

Men with azoospermia, cryptorchidism, or symptoms of infection in genital tract cannot participate in the trial.

**Statistical analyses:**

Changes in the total number of spermatozoa will be compared between the two groups, which are receiving active treatment and placebo treatment, respectively, using relevant statistical analyses.

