**Methods:**

**Design:** The study will be carried out as a randomized, double-blinded, placebo-controlled trial with two arms of equal size.

**Recruitment:** Participants will be reruited via the sperm bank Nordic Cryobank. Participants must be at least 18 years of age. Potential participants will be given written information and a declaration of consent at the sperm bank, and concomitantly they will be offered an elaborating conversation with [name]. If the man – after time to think it over – decides to participate, oral and written consent is obtained. On a regular basis approximately 1-2 men per week are declined as sperm donors in Nordic Cryobank due to reduced semen quality. Men who do not fulfil the donor criteria with respect to sperm count are offered a second semen analysis, and in the case the second sample remains at an equal standard the man is offered participation. Two analysed ejaculates prior to the treatment are required.

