**Number of participants / power estimation:**

With a significance level of 5%, a statistical power of 80%, and a confidence interval of 2 million motile sperm, at least 18 participants should be included in each group ([name], Institute for Biostatistics, AU). However, we request permission to include 100 participants, thus 50 participants per arm.

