**Semen analysis:**

The effect of the treatment is evaluated from measurements of the following classic semen parameters: concentration (sperm/mL), motility, and morphology. The measurements will be performed according to the WHO guidelines (24).

The total number of motile sperm (ejaculate volume x concentration of sperm x per cent of motile sperm) is a combined measure of semen quality. All ejaculates will be discarded immediately after analysis.

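### The stated comparison uses total sperm number but the sample size rests on motile sperm, so the stated 80% power does not apply to the variable tested

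*Protocol*

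**What the plan says.** - Protocol, Statistical analyses: "Changes in the total number of spermatozoa will be compared between the two groups". This is the only between-group comparison stated, and it does not mention motility.
- Protocol, Number of participants / power estimation: 5% significance, 80% power and "a confidence interval of 2 million motile sperm, at least 18 participants should be included in each group". The section then asks for more men: "However, we request permission to include 100 participants, thus 50 participants per arm". It gives no SD and no sidedness, and does not say whether the 2 million is per mL or per ejaculate.
- Protocol, Semen analysis: "The effect of the treatment is evaluated from measurements of the following classic semen parameters: concentration (sperm/mL), motility, and morphology". The same section adds: "The total number of motile sperm (ejaculate volume x concentration of sperm x per cent of motile sperm) is a combined measure of semen quality". It does not call that measure primary or link it to the comparison.
- Protocol, Background: the animal work cited for galangal reports better motility (P < 0.01) and more spermatozoa (P < 0.05). The work cited for pomegranate reports higher concentration (P < 0.01) and better motility (P < 0.05).

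**The concern.** A power statement holds for one variable, with one effect size and one SD. Here it is made for motile sperm, while the comparison is on all sperm, motile and immotile together. No section reconciles the two. An analysis plan that picks either variable must depart from one of the two sections, so this is a contradiction in the protocol and not detail left for later.

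The choice affects what the trial can find. Better motility is one of the animal effects cited for both plants. A treatment that made more sperm motile without raising their number would leave total sperm number unchanged, and the stated comparison would show nothing. A treatment acting partly through motility would be credited only with the part that acts on number. If the choice is left open until results are known, it will no longer be credible.

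**Working it through.** **1. The two variables.** Using the formula in Semen analysis:

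- total sperm number = volume × concentration
- total motile number = volume × concentration × percent motile

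On the log scale, log(total motile) = log(total) + log(percent motile). Percent motile appears only in the second variable.

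**2. The protocol's own figure.** No SD is given, so 18 per group can only be solved backwards. Read the 2 million as the difference to detect, two-sided 5%, 80% power, equal arms, normal approximation:

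SD = 2 / [(1.960 + 0.842) × √(2/18)] = 2 / 0.934 = 2.14 million.

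Other readings give 2.08 (two-sided t), 2.41 (one-sided normal) and 2.36 million (one-sided t). If the 2 million is the half-width of a 95% interval, the SD is 3.06 million; if it is the full width, 1.53 million. The figure of 18 is therefore possible but cannot be verified.

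**3. Does the 80% carry over to total sperm number?** The protocol gives neither an effect nor an SD for that variable. Assume SD 2.14 million for motile sperm and a 50% motile share:

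| Assumption for total sperm number | Effect (million) | SD (million) | Power, 18 per group |
|---|---|---|---|
| Effect and SD both double | 4 | 4.28 | 80% |
| Effect doubles, SD triples | 4 | 6.42 | 46% |
| Effect doubles, SD is four times larger | 4 | 8.57 | 29% |
| Gain confined to motile cells, SD doubles | 2 | 4.28 | 29% (65% at 50 per arm) |

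Among these cases, the 80% is kept only where effect and SD grow by the same factor. The protocol does not claim that they do.

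**4. Illustration at 50 per arm.** Assumptions, none from the protocol: log-normal counts; between-man SD 0.6 to 1.0 and within-man SD 0.4 to 0.5 on the log scale; two samples before and two after treatment. A simulation on that basis gave a residual SD of 0.39 to 0.49, which is used for both variables. Power ≈ Φ(effect / SD × √(50/2) − 1.96).

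- Total motile number, 30% rise: effect log(1.3) = 0.262. With SD 0.49, Φ(2.68 − 1.96) = 76%. With SD 0.39, Φ(3.36 − 1.96) = 92%.
- Total sperm number, half the log-scale rise due to motility: effect 0.131. With SD 0.49, Φ(1.34 − 1.96) = 27%. With SD 0.39, Φ(1.68 − 1.96) = 39%.
- Total sperm number, all of the rise due to motility: effect 0, so the rejection rate is the 5% level.

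A noncentral t calculation lowers these power figures by about one point or less.

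**5. The reverse case.** If treatment acts on number only, the effect is 0.262 on both variables, but total motile number also carries the variation in motility. With an assumed additional log-scale SD of 0.15 to 0.30, its residual SD is between √(0.39² + 0.15²) = 0.42 and √(0.49² + 0.30²) = 0.57. By the t calculation, power is 76 to 91% on total sperm number and 62 to 87% on total motile number.

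**The case against.** **Total sperm number is a defensible outcome.** This stands. The cited animal work also reports more spermatozoa for galangal and higher concentration for pomegranate, and Recruitment selects men who fail the donor criteria on sperm count. A fully null result needs an effect on motility alone, which the cited evidence does not suggest. Step 5 shows that total sperm number can be the more powerful choice.

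**The Statistical analyses section may simply have dropped the word motile.** This is plausible, because Semen analysis defines total motile number and the sample size uses motile sperm. The text does not settle it, and a slip would still need correcting.

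**Three sections name three rival outcomes.** A reader might infer this, but Semen analysis is mainly a measurement section. Concentration and motility are inputs to the counts, and its combined measure agrees with the sample-size basis. The conflict is between two sections.

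**Several variables and two time points leave the error rate uncontrolled.** A reader might infer this too. The protocol states one comparison, and the ranking of other outcomes is commonly left to an analysis plan. Aim sets a three-month treatment period, and The trial presents the ejaculate at 4 to 8 days as a side question about early effect. The documents do not support a multiplicity or time-point criticism.

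**Conclusion.** The point holds in a limited form. The variable in the stated comparison differs from the variable behind the sample size, and nothing in the protocol reconciles them. This rests on the text alone and needs no assumed SD. The stated 80% power therefore does not apply to the comparison as written, and any gain through motility falls outside it.

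The size of the consequence depends on assumptions. With log-scale residual SDs of 0.39 to 0.49 and 50 per arm, power for a 30% rise in motile sperm goes from about 76 to 92% on total motile number to about 27 to 39% on total sperm number when half the rise is due to motility, and to 5% when all of it is. This is one scenario; an effect on number alone reverses the ranking.

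It would be tempting to conclude that the trial is underpowered or that 18 per group is wrong. Neither follows. The 18 cannot be checked without an SD, and the 50 per arm requested is well above it. At the implied SD of 2.14 million, 50 per arm gives 99.7% power for a difference of 2 million motile sperm.

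**What to change.** Name one primary outcome and use it in both Statistical analyses and Number of participants / power estimation, before unblinding.

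- **Simplest route.** Change Statistical analyses to the total number of motile sperm as defined in Semen analysis, measured on the two end-of-treatment ejaculates. This matches the existing power basis. Total sperm number, concentration, motility, morphology and the sample at 4 to 8 days then become supportive.
- **If total sperm number is intended.** Keep Statistical analyses and redo the sample size with an effect and SD for that variable, then restate the sample size and power.

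On either route, state the effect, SD, units and sidedness, so that the figure can be checked.

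The first route costs only protocol wording, because every component is already measured. Its price is that results on the other variables can no longer decide the trial. The second route also needs a source for the SD and a new calculation.

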**Number of participants / power estimation:**

With a significance level of 5%, a statistical power of 80%, and a confidence interval of 2 million motile sperm, at least 18 participants should be included in each group ([name], Institute for Biostatistics, AU). However, we request permission to include 100 participants, thus 50 participants per arm.

**Semen analysis:**

The effect of the treatment is evaluated from measurements of the following classic semen parameters: concentration (sperm/mL), motility, and morphology. The measurements will be performed according to the WHO guidelines (24).

The total number of motile sperm (ejaculate volume x concentration of sperm x per cent of motile sperm) is a combined measure of semen quality. All ejaculates will be discarded immediately after analysis.

**Preparation and dosage of plant components:**

The participants are receiving greater galangal as a dried capsulated ethanolic extract, because the before mentioned animal experiments was based on such extract (2, 3). Pomegranate will be prepared as dried and capsulated juice.

The daily dose of galangal extract will be set at 2 g. This is in fact a lower dose than that used in the experiment with mice (2) (which would give a dose corresponding to 8 g for a man of 80 kg). The lower dose is chosen in order to minimize potential side effects such as gastric irritation, and because the effective dose of the related drogue ginger often is kept at this level (14).

The daily dose of dried pomegranate juice will be set at an amount corresponding to 500 mL of fresh juice. This amount is higher than that used in the before mentioned rat experiment (6) and is thus expected to be sufficient when thriving to reach a measurable effect.

We request that information about the identity, preparation, and dosage of the plant extracts will be kept confidential.

**Risks and precautions:**

Measurements of the chosen semen parameters (concentration, motility, and morphology) are routinely assessed at the location and require no further precautions.

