The effect of pomegranate on semen quality has been addressed in experiments with rats (6), where intake of juice for seven weeks resulted in significantly increased sperm concentration (P < 0.01), improved motility (P < 0.05), and a decreased frequency of abnormal sperm (P < 0.05).

A different experiment on rats showed that a single component from pomegranate, ellagic acid, was able to counteract the negative effect on semen quality caused by cisplatin (7). Also in this study the oxidative balance in semen and serum was significantly improved.

In addition, juice from pomegranate has been shown to improve the oxidative balance in human serum (8, 9), which may be due to a high level of antioxidants, particularly ellagitannins and ellagic acid (10). One of the animal experiments indeed suggests that ellagitannins and ellagic acid play a central role in the improvement of the semen quality (7). The present studies do not indicate any safety risk with the intake of pomegranate (8, 11, 12), only risks of allergic reactions, which may appear following intake of many other fruits (13) cannot be excluded.

*In summary*

We have increased to ingredients, greater galangal and pomegranate, which both may improve semen quality, and which both are approved as food in the EU.

Causes of reduced semen quality

No unambiguous explanation exists to why reduced semen quality has become an increasing problem in Denmark and other western countries (14, 15). Among other factors, smoking during pregnancy (16), hormone disrupting components (17), obesity (18), and oxidative stress (19) have been linked to reduced semen quality.

In this project it is hypothesized that oxidative stress plays a substantial role in the development of reduced semen quality (20). Oxidative stress may appear due to environmental influences or health conditions and can be identified by a high level of reactive oxygen species (21). High levels of reactive oxygen species may damage the sperm membrane and DNA, and as a result the sperm will become defect (22). Oxidative stress may be neutralized by antioxidants, which inhibit the formation of reactive oxygen species (19).

Greater galangal and pomegranate both contain a high level of various antioxidants (23, 10). It is therefore reasonable to assume that these two ingredients have the ability to neutralize oxidative stress and as a result improve semen quality.

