**The trial:**

When a potential participant has been given oral and written information about the trial and given his written consent, biostatistician professor [name] will randomize him to get tablet containing either extracts of pomegranate and greater galangal or placebo tablets. The participant will concomitantly receive a questionnaire, which he is encouraged to fill out and return just prior to the cure. At the end of the three months of daily intake of tablets the participants will deliver two ejaculates with 4-10 days of interval. The treatment will be continued until the last ejaculate is delivered.

In addition to the start- and end-ejaculates, the participants are asked to deliver one ejaculate 4-8 days after treatment start to provide information on whether a possible effect can be measured after a short treatment time.

The ejaculates can be collected in Aarhus (where many of the potential participants expectedly live) but will be examined in the laboratory of Scientific Unit of Reproduction Biology, Horsens Regional Hospital. With the delivery of the last ejaculate the participant will receive kr. 1500 corresponding to kr. 300 per ejaculate. If a participant leaves the trial before the three months have passed, he will receive kr. 300 per delivered ejaculate. An experienced laboratory technician will together with [name] manage: the recruitment of participants, informing the participants about the trial, handling the hand-over of tablets, and administrating and coordinating the hand-in and analysis of ejaculates. The fact that the practical work is all handled by one experienced laboratory technician ensures that all analyses are carried out as similarly as possible.

The active treatment consists of a daily intake of 2x 1 gram of dried ethanolic extract of greater galangal and dried pomegranate corresponding to 500 mL of fresh pomegranate juice. The extracts are standardized from HPLC-measures of marker components. Both extracts are given as tablets. The placebo treatment holds daily intake of a corresponding number of tablets containing inactive components.

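### Allergy and gastric irritation are named as possible effects of the tablets, but known allergy is not excluded, the risk section omits both effects, and no symptoms are asked about after the start

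*Protocol*

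**What the plan says.** Two possible effects of the tablets are named. In Protocol, Background, the review of pomegranate safety ends with the reservation "only risks of allergic reactions, which may appear following intake of many other fruits (13) cannot be excluded". In Protocol, Preparation and dosage of plant components, the galangal dose is explained thus: "The lower dose is chosen in order to minimize potential side effects such as gastric irritation".

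Protocol, Risks and precautions, consists of one sentence: "Measurements of the chosen semen parameters (concentration, motility, and morphology) are routinely assessed at the location and require no further precautions". The ethics section lists the delivery of several samples as the only inconvenience.

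On who may enter, Protocol, Inclusion criteria, says "The only inclusion criteria are that the men should have a semen quality below semen donor level and be otherwise healthy", and Protocol, Exclusion criteria, says "Men with azoospermia, cryptorchidism, or symptoms of infection in genital tract cannot participate in the trial".

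On contacts, Protocol, The trial, describes one questionnaire: "a questionnaire, which he is encouraged to fill out and return just prior to the cure". After the start, "the participants are asked to deliver one ejaculate 4-8 days after treatment start", and two more ejaculates follow at the end of three months, 4 to 10 days apart. On stopping, "The treatment will be continued until the last ejaculate is delivered".

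**The concern.** The protocol identifies two hazards of the product, but the sections that should act on them do not. The risk section discusses the laboratory measurement and not the tablets. The eligibility rules would admit a man who knows that he is allergic to pomegranate. Once tablets are being taken, nobody is scheduled to ask how they are tolerated.

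Two things are at stake. The first is the safety of an allergic participant, who could be allocated daily pomegranate for more than three months. The second is information. Protocol, Aim, looks for a treatment that can be put to use, and a reader of the results will want to know how men tolerated it. Symptoms that were never asked about cannot be supplied later by an analysis plan, so this is not a detail that an unseen plan could settle. Eligibility and data collection belong in the protocol.

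**Working it through.** The protocol gives no figure on this point to reproduce, so the check is mainly a comparison of sections.

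**1. Each named effect against each safeguard.**

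| | Pomegranate: allergy | Galangal: gastric irritation |
|---|---|---|
| Named as possible | Yes (Background) | Yes (Preparation and dosage) |
| Mentioned in Risks and precautions | No | No |
| Lowered dose | No | Yes |
| Screening of individual men | No | No |
| Symptom question after the start | No | No |

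The pomegranate dose was not lowered. Protocol, Preparation and dosage of plant components, sets it above the amount in the rat experiment.

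**2. Is a known allergy excluded in other words?** The three exclusions concern sperm absence, undescended testis and genital infection. The only remaining candidate is the requirement of general good health in the inclusion criteria. A man with a fruit allergy and no other complaint would usually call himself healthy, so that wording does not reliably exclude him.

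**3. Contacts after the start.** The full payment is kr. 1500 at kr. 300 per ejaculate:
- 1500 / 300 = 5 ejaculates
- 5 − 2 before treatment = 3 after the start (one at 4 to 8 days, two at the end)

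All three are described only as sample deliveries, and Protocol, Semen analysis, evaluates semen parameters only. The single questionnaire comes back before the first tablet. Symptom questions planned after the start: 0 at 3 contacts.

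**4. How long a man would take the tablets.** Assume that three months is 90 days, that the first end sample falls on day 90, and that the second follows 4 to 10 days later with tablets continuing until then:
- shortest: 90 + 4 = 94 days
- longest: 90 + 10 = 100 days

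**5. The gap between contacts.** Between the early sample and the first end sample:
- 90 − 8 = 82 days
- 90 − 4 = 86 days

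So forms at the existing samples would leave more than 80 days with no scheduled contact. They can record symptoms from recall, but they cannot serve as an alarm. A direct contact route is needed as well.

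**6. What the cited safety evidence covers.** Background states that no safety risk is indicated for galangal and gives two references. The text describes one as a mouse experiment, and the title of the other names mice. Neither can speak to stomach complaints in men. For pomegranate, human studies are cited, and the same sentence leaves allergy open.

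**The case against.** The strongest reply is that safety was considered. Background required each extract to be permitted as food in Denmark or the EU and to have shown no serious side effects in earlier trials. The galangal dose was set well below the mouse equivalent (2 g against 8 g for a man of 80 kg) and in line with usual ginger doses. This stands, and it lowers the expected risk. It does not close the gap: these steps select the extracts and the dose, not the men, and food approval does not protect someone allergic to that food.

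A second reply is that the participant information and the content of the baseline questionnaire are not shown. Either might mention allergy, and the ethics section promises full oral and written information with some weeks before consent. This is possible and cannot be checked. Advice to participants would still be neither an exclusion criterion nor a record of symptoms.

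A reader might infer more than the documents support:
- **That allergic men will be enrolled or harmed at some rate.** No allergy frequency is given. The equal arms fix only the chance of active treatment, which is not a risk of harm.
- **That men will not be told what they take**, because the sponsor asks for confidentiality about the extracts. The protocol does not say that this applies to participants, and the ethics section points the other way.
- **That the trial could say nothing about tolerability.** Payment per delivered sample allows early leaving to be counted by arm, though not the reasons for it.
- **That the efficacy result is biased.** Nothing here affects the comparison of sperm numbers.

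**Conclusion.** The point holds as a safety and data-collection gap of modest size. Both effects are named by the protocol itself; the risk section covers neither; known allergy to an ingredient is not a bar to entry; and none of the three contacts after the start includes a symptom question. On the stated criteria, an allergic man could be given pomegranate tablets daily for about 94 to 100 days, if three months is taken as 90 days.

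How often that would happen cannot be estimated from the document, and the expected risk is low given how the extracts were selected. The conclusion does not depend on such an estimate. It assumes that the sections shown are complete on eligibility, contacts and risks, which is where this content would belong. The change is worth making because it protects participants at little cost and because symptom data that are not collected are lost for good.

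**What to change.** 1. **Exclusion criteria.** Add: *Men with known allergy to any ingredient of the tablets cannot participate.*
2. **The trial.** Add a brief form on gastric and allergic symptoms, the same in both arms, at baseline (with the existing questionnaire) and at the three existing samples after the start. Men hand it in sealed. Nobody involved in the semen analysis opens it until that man's analyses are complete. The seal matters because the technician and the colleague who manages participants also handle the hand-in and analysis of samples, so neither is an independent recipient.
3. **Risks and precautions.** Name gastric irritation and allergic reaction as possible effects of the tablets. Tell men to stop the tablets and contact a named study role at once if an allergic reaction occurs, and still invite them to give the end samples. This route covers the 80 or more days between contacts, which a sealed form cannot do.

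**Cost.** No extra samples, visits or sample size are needed; a few men may be turned away for allergy. Four forms per man give 100 × 4 = 400 forms. At an assumed 5 minutes each, completion takes 400 × 5 / 60 = 33 hours in total, or 20 minutes per man (20 hours in total at 3 minutes, 67 at 10). With the minimum of 36 men it is 144 forms and 12 hours (7 to 24). Data entry, review and tabulation come on top and must fit a fixed grant with 10 hours of statistical help, so the form should be short. A small risk of unblinding remains, because men may mention symptoms when they deliver samples.
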